### Measures

The Warwick-Edinburgh Mental Wellbeing Scale (WEMWBS) was selected as the primary outcome measure as it captures the broader adjustment and quality of life outcomes that VaLiANT targets, and the majority of participants displayed reliable and clinically significant improvements on the measure during the Phase I evaluation of VaLiANT (55). The WEMWBS is a 14-item questionnaire that measures the frequency of positive mental health and wellbeing over the previous 2 weeks (64). Items such as “I've been feeling optimistic about the future” are rated on a 5-point Likert scale with higher scores indicating greater wellbeing (total score range 14–70). The scale demonstrates good internal consistency (0.91), test-retest reliability (0.83), and criterion validity (64) and has been used in a previous ABI RCT (51).

The Valued Living Questionnaire – Comprehension Support version (VLQ-CS^1^) was developed by members of the research team as an adaptation of the original VLQ, following evidence that multiple comprehension errors were made by people with ABI on the original measure^2^. The VLQ-CS is designed to suit to the needs of individuals with cognitive and/or communication difficulties, and includes visual communication supports, simplified instructions and examples of value-consistent behaviors to aid understanding. Ten value domains (e.g., family, work) are rated for importance on a 10-point scale (higher scores = higher importance). For domains with an importance rating ≥5, the extent to which time spent on value-consistent behaviors in that domain over the last week was “ideal” is then rated on a 10-point “consistency” scale (higher scores = more ideal). A composite score is derived by calculating the mean of the products of the importance and consistency scores. The VLQ-CS has been validated for use with ABI with greater test-retest reliability than the original measure ^1^.

Mood is assessed with the Hospital Anxiety and Depression Scale [HADS; (65)] and the Depression Anxiety Stress Scales [DASS-21; (66)]. The inclusion of both measures was based on previous research in brain injury which indicated that the HADS-A is more sensitive to clinically relevant symptoms of anxiety while the DASS-D is more sensitive to clinically relevant symptoms of depression (67).

All other sample characterization measures and secondary outcome measures are summarized in Table 3.

**Table 3 T3:** Timing of outcome measures.

**Outcome domain**	**Measure**	**T1**	**T2**	**T3**
**Sample characterization**
Premorbid intellectual ability	Test of Premorbid Functioning (68)	X		
Verbal memory	Rey Auditory Verbal Learning Test (69)	X		
Cognitive flexibility^*^	Trail Making Test—written (70) and oral (71) versions	X		
Idea generation	Controlled Oral Word Association Test (72)	X		
Treatment expectancy	The Credibility/Expectancy Questionnaire (73)	X		
**Primary outcome**
Wellbeing	The Warwick-Edinburgh Mental Wellbeing Scale (64)	X	X	X
**Secondary outcomes**
Mood	Hospital Anxiety and Depression Scale (65)	X	X	X
	Depression Anxiety Stress Scales – 21 (66)	X	X	X
Valued living^**^	Valued Living Questionnaire – original (74) and comprehension support^1^ version	X	X	X
	Valuing Questionnaire (44)	X	X	X
Psychological flexibility	The Acceptance and Action Questionnaire after brain injury (75)	X	X	X
Quality of life^**^	World Health Organization Quality of Life scale (76)	X	X	X
Psychological adjustment^**^	The Head Injury Semantic Differential Scale – III (77)	X	X	X
Community participation^**^	The Community Integration Questionnaire – original (78) and revised (79) versions	X	X	X
Post-traumatic growth	The Changes in Outlook Questionnaire – Short form (80)	X	X	X
Cognitive strategy use	Self-report strategy use checklist (81)	X	X	X
Subjective memory functioning	The Everyday Memory Questionnaire – Revised (82)	X	X	X
Self-Efficacy	The TBI Self-Efficacy Scale (83)	X	X	X

*T1, baseline assessment; T2, 8-week follow-up assessment; T3, 16-week follow-up assessment*.

* *Indicates measures that were adapted to be deliverable via telehealth*.

** *Indicates measures that were included or adapted following trial commencement*.

### Feasibility and Acceptability Measures

Feasibility of the trial design will be assessed against the following criteria: 1) recruitment of the minimum number of participants required to run quarterly groups throughout the study period (minimum of 3 participants per group); 2) acceptable participant drop-out rates in intervention and control conditions (<20%); 3) adequate outcome assessment completion rates (≥80%); and 4) successful blinding of outcome assessors (≥90%). Consistent with the Phase I study (55), feasibility of the intervention will be assessed against: 1) group attendance rates (≥80% overall participant attendance); 2) and homework completion rates (≥50% completion rate for participants in attendance for each session). Acceptability of the intervention is measured by asking participants to rate their level of confidence in recommending the VaLiANT program to a friend who experiences similar problems (1 = “Not at all confident,” 9 = “Very confident”). The intervention will be deemed “acceptable” if the mean rating is ≥80% (i.e., ≥7.2/9).

### Randomization and Blinding

Randomization is performed by a researcher independent from the study using an online generator known as Research Randomizer (https://www.randomizer.org). Eligible participants are randomly assigned to the intervention condition or control condition with an allocation ratio of 2:1 (Intervention: Control). This allocation ratio was selected to optimize recruitment rates and maximize the number of people experiencing the intervention to allow for exploration of treatment dimensions and predictors of outcome (84, 85). Randomly permuted block sizes of 3, 6, or 9 are used to ensure a balanced allocation ratio. Group allocation is concealed, either in sequentially numbered sealed opaque envelopes (pre-COVID) or electronically *via* sequentially numbered word-documents uploaded to a protected cloud-sharing platform (post-COVID), which are opened at the end of the baseline (T1) assessment. The outcome assessors at T2 and T3 are research assistants blinded to condition allocation. Participants are reminded to not disclose their allocation during assessments, and all instances of unblinding are recorded. If unblinding occurs during a T2 assessment, then a different blinded research assistant conducts that participant's T3 assessment.

### Procedure

The VaLiANT group is planned to run quarterly with an associated participant intake period prior to commencement of each group. Potential participants undergo screening to ensure eligibility before informed consent is obtained. For each intake, all eligible participants attend an initial baseline assessment (T1) which includes all baseline sample characterization measures and primary and secondary outcome measures. Randomization occurs immediately following the T1 assessment. In addition to their usual care, participants in the treatment condition then attend the 8-week VaLiANT group program at the La Trobe University Psychology Clinic, or *via* telehealth (Zoom videoconferencing) during periods of COVID-19 restrictions, while control participants undergo treatment-as-usual (i.e., their usual care). Participation in other treatment during the trial is documented, including the frequency and type of treatment. VaLiANT group sessions are facilitated by an experienced clinical neuropsychologist with assistance from two trainee psychologists. All sessions are video-recorded. Outcome assessments occur within 1–2 weeks following the intervention/waiting period (T2), and at an 8-week follow-up (T3). All assessments take roughly 90 min and are administered by assessors blinded to condition allocation. Assessments are conducted at the La Trobe University Psychology Clinic or in participants' homes if preferable. During periods where COVID-19 restrictions apply, assessments are conducted over Zoom videoconferencing.

### Data Management

During the trial, hard copy information is stored at La Trobe Psychology Clinic in a locked cabinet while electronic information is stored on secure electronic databases, accessible only by the project coordinator, chief investigator, and research assistants. Prior to data analysis, all values will be checked for plausibility. Data will be retained for 7 years after completion of the project and then destroyed by securely deleting electronic records (including video and audio recordings) and shredding all paper records.

### Sample Size Calculation

A power analysis was conducted using 5,000 simulations within the SimR package for R (86) to determine if the maximum possible sample size during the data collection period (*N* = 64) was sufficient for the statistical analyses. A previous evaluation of an ACT-based intervention following stroke reached a moderate group-by-time effect (η2 = 0.07) on the Warwick and Edinburgh Mental Wellbeing Scale (51). Accordingly, a minimum sample of 52 participants is required to achieve statistical power for a linear mixed-effect model with a 2 (group) x 3 (time) design (80% power, α = 0.05). Allowing for an attrition rate of 10%, an N of 58 is adequate to perform the primary analyses.

### Statistical Analysis

Main analyses will follow an intention-to-treat approach. Little's missing completely at random (MCAR) analysis will be conducted to determine if data are MCAR (87). If <5% of data is MCAR, the appropriate data imputation technique will be employed to deal with missing values [likely Markov chain Monte Carlo method; (88)]. Univariate outliers (z +/− 1.96 SD) will be adjusted using a winsorising solution (89). Univariate checks of normality (skewness > +/− 2.58 SD) will be conducted, and variables that violate the criterion will be corrected to normal using appropriate data transformation (90). Primary and secondary outcomes will be analyzed with linear mixed models, with fixed effects of time and group, and participants modeled as random effects. The estimated marginal means from the model will be used to calculate effect sizes (Cohen's *d*) to illustrate change in both between group and timepoint contrasts. The results of the fixed effects estimates for the main effects and interaction terms will be presented as standardized *B* values and all analyses will use a two-sided alpha level of 0.05. These analyses will be conducted using JASP (91). Finally, as an adjunct to the linear mixed models, the Crawford and Howell measure of reliable change (92), which is suitable for serial testing, will be calculated for the primary outcome (93). The proportion of participants achieving reliable change in each group at both time-points will then be compared with 2 × 2 Chi square tests of independence.

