Compare the impact of VaLiANT against treatment-as-usual waitlist control on a range of adjustment-related outcomes including at the levels of impairment, activity, participation, and overall wellbeing and quality of life. This will identify signals of efficacy and determine parameter estimates for a definitive Phase III trial.Investigate the feasibility of the trial design, including recruitment rate, retention rate, success of blinding the outcome assessor under RCT conditions, and exploring the fidelity of delivering the intervention.

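### Winsorising every score beyond ±1.96 SD changes about 5% of valid scores by construction, and so shrinks the SD and, on pooled data, the raw group difference that Phase III would draw on

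*Protocol article*

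**What the plan says.** In the Protocol article, Statistical Analysis sets out data preparation before any model is fitted. After the handling of missing values comes the outlier rule: "Univariate outliers (z +/− 1.96 SD) will be adjusted using a winsorising solution (89". A skewness check with a threshold of 2.58 follows, and "variables that violate the criterion will be corrected to normal using appropriate data transformation (90". The outcomes then go into linear mixed models "with fixed effects of time and group, and participants modeled as random effects". For effect sizes, "The estimated marginal means from the model will be used to calculate effect sizes". The section names no analysis of the unaltered scores. It does not say whether z is computed over all participants or within arm, which value replaces an outlier, or whether the reliable-change analysis uses adjusted scores.

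Three other places bear on the point. Data Management says: "Prior to data analysis, all values will be checked for plausibility". Measures describes the primary outcome, the Warwick-Edinburgh scale (WEMWBS), as a bounded questionnaire total ("total score range 14–70"). The first aim, at the end of the Introduction, says of the comparison with control: "This will identify signals of efficacy and determine parameter estimates for a definitive Phase III trial".

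**The concern.** A cut-off of ±1.96 SD does not separate unusual scores from ordinary ones. In a perfectly normal variable, one score in twenty lies beyond it. By the time the rule is applied, implausible values have been screened out and the scale cannot produce a total outside 14 to 70. What the rule changes is therefore mostly genuine patient responses.

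Pulling in both tails reduces the SD, and can reduce the difference between arms. Both are quantities that a Phase II trial passes to the planning of Phase III, which is one of this trial's stated purposes.

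The normality rule has a separate fault. A linear mixed model assumes roughly normal residuals and random effects, not normal raw scores. Raw scores can be skewed while the residuals are acceptable. Once a variable is transformed, its estimates are no longer in WEMWBS points, which are the natural unit for a Phase III target difference.

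**Working it through.** **The plan's own figure.** The plan gives no number for the effect of winsorising. Its sample size (Sample Size Calculation) is 52 inflated for 10% attrition: 52/0.9 = 57.8, so 58, as stated. At the 2:1 allocation this is 39 and 19 participants, used below.

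**Scores altered (normal data).** P(|z| > 1.96) = 0.05. Expected number per visit: 58 × 0.05 = 2.9. Over three visits: 8.7. Chance of at least one at a given visit: 1 − 0.95^58 = 0.949.

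**Variance after clipping a standard normal at c = 1.96.** With Φ(c) = 0.975 and φ(c) = 0.0584:

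Var = (2Φ(c) − 1) − 2cφ(c) + 2c²(1 − Φ(c)) = 0.950 − 0.229 + 0.192 = 0.913

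SD ratio = √0.913 = 0.955.

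**Difference, SD and Cohen's d together.** Simulation of 8,000 trials per scenario, 39 v 19, one visit. The assumed true d is 0.549, from the plan's η² of 0.07: f = √(0.07/0.93) = 0.274 and d = 2f. Entries are ratios to the unaltered analysis, for z computed on the pooled sample.

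| Data | Outlier replaced by | Raw difference | SD | d |
|---|---|---|---|---|
| Normal | cut-off | 0.959 | 0.960 | 0.999 |
| Normal | nearest retained score | 0.935 | 0.939 | 0.995 |
| Heavy-tailed (t, 5 df) | cut-off | 0.955 | 0.900 | 1.052 |
| Heavy-tailed (t, 5 df) | nearest retained score | 0.932 | 0.868 | 1.065 |
| Skewed (gamma) | cut-off | 0.963 | 0.896 | 1.072 |
| Skewed (gamma) | nearest retained score | 0.951 | 0.870 | 1.090 |

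Winsorising within arm leaves the raw difference nearly unchanged. It raises d by 4–8% for normal data and 9–18% otherwise. Type I error is 6–9% within arm, against about 5% when pooled.

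**Repeated visits.** With correlated visits (39 v 19, assumed correlation 0.5 and 0.7, baseline-to-T2 change), pooled winsorising took the difference in change from 0.547 to 0.525 and from 0.551 to 0.529, about 4% less in each case. The SD of change fell by about 3–4%. Six to seven of 58 participants had at least one score altered.

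**Phase III.** Sample size is proportional to (SD/difference)².

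- Shrunken SD with an external target difference: the factor is 0.913, so about 9% too few. For an assumed difference of 4 points and SD of 10, this gives 90 per arm instead of 99, and true power of 76.5% instead of 80%.
- Shrunken SD with the shrunken difference from the same analysis (pooled, normal, cut-off): (0.960/0.959)² = 1.002, so essentially no change.

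**The case against.** The strongest reply is that the harm largely cancels. The plan reports Cohen's d and standardised coefficients. With pooled z and normal data, the difference and the SD shrink almost equally, so d and the type I error are preserved. This stands, and it limits the Phase III shortfall to the case where the SD from this trial is paired with a difference from elsewhere. The aims speak of parameter estimates and do not name the SD. Still, the SD is a core planning parameter for a continuous outcome, and pairing it with a clinically chosen difference is routine.

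Second, the bias is small beside the sampling error. With 56 degrees of freedom the 95% interval for an SD runs from about 0.84 to 1.23 times the estimate. That is correct and bears on priority. But the bias is systematic, it is introduced by the analysis itself, and it costs almost nothing to remove.

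Third, winsorising is meant to limit the influence of extreme scores, not to repair errors, so a prior plausibility check does not make it redundant. This also stands. The fault is a cut-off that catches 5% of well-behaved data, with no analysis of the unaltered scores named beside it.

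A reader might infer more than the document supports:

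- **Inflated effect sizes and type I error.** The larger figures need within-arm winsorising, which the text does not state. A univariate rule reads more naturally as applied to each variable over the whole sample. The inflation under pooling needs heavy tails or skew, which are assumed here.
- **The largest improvers and decliners are pulled in.** The rule acts on the level of a score at a visit, not on change. In simulation, only about 16–27% of the six largest changers among 58 had either score altered (assumed T1–T2 correlation 0.5 to 0.83), and a repeat gave about 14–25%. Nor does the text say that reliable change uses winsorised scores.
- **Transformation shrinks the SD, or puts visits on different scales.** Transformation applies only if the skewness criterion is violated. It changes the scale rather than shrinking the SD as such, and the text does not say that visits would be transformed separately.

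**Conclusion.** The point holds in a limited form. The ±1.96 SD rule, as written, alters about 5% of valid scores. For normal data with replacement at the cut-off, it lowers the SD by 4–5% and, with pooled z, the raw difference by about 4%, while d stays essentially the same. The direction of any bias in d depends on the shape of the data and on details that the text leaves open. The Phase III shortfall of up to about 9% rests on pairing the shrunken SD with an unshrunken difference. The relative figure does not depend on the assumed 4 points and SD of 10.

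The checks use single-visit and change-score comparisons, not the full planned mixed model. The normality rule is aimed at the wrong quantity, since it examines raw variables rather than residuals, but no size can be put on that. The analysis section should be corrected. The effect is too small to call the trial's conclusions unsafe.

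**What to change.** Rewrite the outlier and normality sentences in Statistical Analysis as follows:

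- The primary analysis uses scores as recorded. Only values impossible for the scale, or traced to a recording error, are corrected.
- Normality is assessed on the residuals and random effects of the fitted mixed model, not on raw variables.
- Cohen's d, the SDs reported for Phase III planning, and reliable change are calculated from unaltered scores.
- Winsorised, transformed, and robust or bootstrap results are sensitivity analyses. If winsorising is kept there, state whether z is pooled or within arm and which value replaces an outlier.

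The cost is wording only, with no extra participants, visits or measures. Intervals will be slightly wider, because the variance is no longer reduced by the rule.

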### Study Design

This Phase II pilot study is a prospectively registered single center, two-arm, assessor-blinded, parallel groups RCT, comparing outcomes of the 8-week VaLiANT group intervention with treatment-as-usual waitlist control. Outcome measures are collected at baseline (T1), at an 8-week follow-up (T2), and at a 16-week follow-up from baseline (T3). An overview of the study procedure is summarized in Figure 1. This protocol was developed in accordance with the Standard Protocol Items: Recommendations for Interventional Trials (SPIRIT) guidelines (56). Methodological modifications made due to the impact of COVID-19 have been reported in line with SPIRIT Extension for RCTs Revised in Extenuating Circumstances (CONSERVE-SPIRIT) guidelines (57) throughout the text and summarized in a separate paragraph. The methodological quality of the trial will be evaluated using the Physiotherapy Evidence Database – Psycbite (PEDro-P) scale upon completion of the trial (58).

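### The planned 2 × 3 mixed model leaves the pre-randomisation T1 arm difference free, which costs about 8–25% of the treatment contrast's variance, and an intercept-only random effect could misstate the T2 and T3 standard errors

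*Protocol article*

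**What the plan says.** Under Statistical Analysis, the protocol article says: "Primary and secondary outcomes will be analyzed with linear mixed models", "with fixed effects of time and group, and participants modeled as random effects". An interaction is part of the model, because "The results of the fixed effects estimates for the main effects and interaction terms will be presented as standardized" B values. Estimated marginal means are then used to derive Cohen's d for differences between arms and between visits, and "all analyses will use a two-sided alpha level of 0.05".

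Sample Size Calculation describes the same model as a "linear mixed-effect model with a 2 (group) x 3 (time) design". Study Design lists only three assessments (baseline, 8 weeks and 16 weeks), so the three time levels must be T1, T2 and T3. Procedure states: "Randomization occurs immediately following the T1 assessment".

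The article mentions no baseline covariate and no constraint on the T1 means. It does not say whether the participant effect is an intercept only, and it names no residual covariance structure.

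**The concern.** Two features of this model deserve a check.

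**The free T1 difference.** Allocation follows the T1 assessment, so any T1 difference between arms is chance. A model with a group main effect and a group × time interaction still estimates that difference and subtracts it in full from the T2 and T3 differences. Baseline adjustment subtracts only the part that T1 predicts. The sample has a stated ceiling of 64 and 2:1 allocation, hence about 64/3 ≈ 21 controls. Precision that can be had from a score already collected is therefore worth having, particularly as one stated aim is to supply parameter estimates for a Phase III trial.

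**One common correlation.** A participant random intercept with independent residuals forces the same correlation on every pair of visits. If T1 and T3, sixteen weeks apart, correlate less than adjacent visits, one pooled standard error is applied to contrasts whose true variances differ.

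**Working it through.** **Inputs from the protocol article.** Three visits; group, time and interaction; T1 before randomisation; two-sided α = 0.05; 80% power; minimum N = 52, or 58 with 10% attrition; 2:1 allocation, so 35 and 17 at N = 52. The only correlation given for the primary scale is a test-retest reliability of 0.83 (Measures), without an interval.

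**Assumed.** The between-visit correlation ρ, taken from 0.5 to 0.83, and equal variance σ² at each visit.

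**The plan's own figure.** 52/0.9 = 57.8, so 58 reproduces. The 52 comes from a simulation whose variance components and mean pattern are not given, so it cannot be rebuilt uniquely. Nothing below depends on it being right or wrong.

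**Step 1: efficiency.** Let k = σ²(1/n₁ + 1/n₂).

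- Free T1, difference in change: variance = 2(1−ρ)k
- T1 constrained or adjusted for: variance = (1−ρ²)k
- Ratio = (1−ρ)(1+ρ) / [2(1−ρ)] = (1+ρ)/2, so the saving is (1−ρ)/2

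The standard error saving is 1 − √((1+ρ)/2). The equivalent N is 52(1+ρ)/2. The power column assumes that the free-T1 contrast has exactly 80%.

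| ρ | Variance ratio | Variance saved | SE saved | N equivalent to 52 | Power, from 80% |
|---|---|---|---|---|---|
| 0.5 | 0.750 | 25% | 13.4% | 39 | 90% |
| 0.6 | 0.800 | 20% | 10.6% | 42 | 88% |
| 0.7 | 0.850 | 15% | 7.8% | 44 | 86% |
| 0.83 | 0.915 | 8.5% | 4.3% | 48 | 83% |

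A generalised least squares calculation gives the same ratios. In 20,000 simulated trials with 35 and 17 participants, estimating the baseline slope took back a little of the gain. The ratio at T2 was 0.818 rather than 0.800 at ρ = 0.6, and 0.929 rather than 0.915 at ρ = 0.83.

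**Step 2: common correlation.** With complete data, the random-intercept model bases every change contrast on the mean correlation ρ̄ of the three visit pairs. The true variance uses that pair's own correlation. Hence model SE / true SE = √[(1−ρ̄)/(1−ρ_pair)].

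For T1T2/T1T3/T2T3 = 0.7/0.6/0.7, ρ̄ = 0.667:
- T3: √(0.333/0.4) = 0.913
- T2: √(0.333/0.3) = 1.054

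For 0.7/0.5/0.7, ρ̄ = 0.633:
- T3: √(0.367/0.5) = 0.856
- T2: √(0.367/0.3) = 1.106

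Simulated type I error at nominal 5%, free-T1 random-intercept model, 35 and 17 participants, complete data:

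| T1T2/T1T3/T2T3 | T2 contrast | T3 contrast | Omnibus interaction |
|---|---|---|---|
| 0.7/0.6/0.7 | 3.7% | 7.2% | 5.5% |
| 0.7/0.5/0.7 | 3.1% | 9.2% | 5.4% |
| 0.6/0.6/0.6 | 4.8% | 5.1% | not run |

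Repeat simulations differed by at most about 0.3 percentage points. A high correlation does not by itself protect T3: 0.83/0.75/0.83 gave 8.5% at T3 and 3.6% at T2.

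**The case against.** The strongest reply is that nothing here is an error. A difference-in-change contrast is unbiased under randomisation and is a standard analysis. The sample size was simulated for a mixed model of the same 2 × 3 form, so no power is shown to be lost against the plan. The trial is a Phase II feasibility study. All of that stands: a reader might infer that the free T1 term biases the result or leaves the trial underpowered, and the article supports neither inference.

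The size of the loss is also open. A reader might take 15–25% as a property of this trial. That range is a variance figure and needs ρ between 0.5 and 0.7, which the article does not give. Its one figure, 0.83, yields 8.5%. Retest reliability may well overstate an 8- or 16-week correlation, so 0.83 serves as the upper end of the range considered rather than as an estimate.

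On the second part, the objection narrows the claim a good deal. The wording on participants as random effects suggests an intercept but does not say so, and a fuller plan may settle the covariance. The power target is the group-by-time effect, no T3 test is named as primary, and the omnibus test holds close to 5%. To say flatly that the T3 error rate is inflated would go beyond the document.

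One part of the objection does not carry: that baseline handling was simply left to a fuller plan. The article states the 2 × 3 form with main effects and interaction in two sections, and that form leaves the T1 difference free.

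**Conclusion.** The point holds as a matter of efficiency, with a conditional warning on standard errors.

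- **Efficiency.** The stated model gives an unbiased treatment contrast with more variance than necessary. The avoidable part is (1−ρ)/2, about 8–25% for assumed ρ from 0.83 to 0.5 (4–13% of the standard error), less slightly over one percentage point of variance for estimating the slope at this sample size. The direction is certain for any ρ below 1; the size rests on the assumed ρ.
- **Standard errors.** If the random effect is an intercept only and correlation falls with time, the T3 standard error is understated by about 9–14% in the two main patterns (type I error about 7–9%) and the T2 one is overstated (about 3–4%). With equal correlations there is no distortion. The omnibus interaction is almost unaffected in the decaying patterns tried. The exposure is therefore confined to visit-specific contrasts and coefficients, which the plan does intend to report.

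This is an improvement worth making before analysis. It does not show that the planned analysis is invalid.

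**What to change.** Replace the model statement with a constrained longitudinal model: T1, T2 and T3 as outcomes, one common T1 mean for both arms, time effects, group × T2 and group × T3 effects, and an unstructured 3×3 covariance across visits. Alternatively, model T2 and T3 with T1 as covariate and let its slope differ by visit. The two are close but not identical when T1 is missing, so name one.

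Apply it to the primary outcome and to each secondary scale given in the same version at T1. The scales added or replaced after the trial began (valued living, quality of life, psychological adjustment, community participation) need a sentence on which participants have a usable T1 score.

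The cost is a change of wording and four extra covariance parameters (six for an unstructured 3×3 matrix against two for a random intercept plus residual). If JASP cannot fit the model, it can be run in R, which was already used for the power simulation. No new data are needed.
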